## Abstract

**Introduction:**

Cognitive impairment is a major source of disability in neurodegenerative conditions, and it is also highly prevalent in autism spectrum disorder and attention-deficit/hyperactivity disorder. Across these conditions, subclinical epileptiform activity and resting-state functional hyperactivity have been repeatedly described, suggesting a shared state of cortical hyperexcitability. The LENDÜLET Neurocognitive Research Project aims to determine the incidence and multimodal characteristics of cortical hyperexcitability in multiple patient populations and to elucidate how hyperexcitability relates to cognitive performance, large-scale network connectivity, sleep-dependent memory consolidation, and tau/amyloid burden.

**Methods:**

In a prospective, multimodal observational study, we are recruiting 75 participants per group (patients with mild cognitive impairment, patients with autism spectrum disorder, patients with attention deficit/hyperactivity disorder, and healthy controls; total *N* = 300) at the National Institute of Psychiatry and Addictology (Budapest, Hungary). All participants are undergoing a harmonized diagnostic protocol including detailed neuropsychological assessment, structural MRI, resting-state functional MRI, and 24-h ambulatory electroencephalography. Patients with neurodegenerative conditions will additionally undergo CSF sampling. Individuals who exhibit markers of cortical hyperexcitability will be invited to an in-ward mechanistic substudy (3-day video-electroencephalography monitoring with repeated neuropsychological paradigms, overnight sleep recordings, and spindle analysis, and serial blood sampling to characterize circadian dynamics of tau and amyloid.

**Anticipated results:**

Primary outcome is the incidence and distribution of cortical hyperexcitability in each diagnostic group relative to controls. Secondary outcomes include relationships between hyperexcitability and (a) structural atrophy and white matter integrity; (b) functional connectivity within and between default mode, salience, and attention networks; (c) cerebrospinal and plasma tau/amyloid levels; and (e) domain-specific cognitive performance. The current paper describes the study design, while the results are not reported.

**Discussion:**

This study will provide the first systematic, multimodal assessment of cortical hyperexcitability across multiple neurocognitive disorders with shared vulnerability to epilepsy and cognitive decline. The resulting biomarker panel may support risk stratification, inform clinical trial design for anti-hyperexcitability interventions, and ultimately enable individualized prevention strategies for cognitive decline.

## Introduction

1

### Rationale

1.1

Cognitive deterioration is a core feature of major neurocognitive disorders (NCD), particularly mild cognitive impairment (MCI) and Alzheimer’s disease (AD), but is also highly prevalent in autism spectrum disorder (ASD) and attention-deficit hyperactivity disorder (ADHD) (Leffa et al., 2023; Torenvliet et al., 2023). The cumulative prevalence of these conditions approaches 20% in developed societies, imposing a substantial medical, social, and economic burden. While these disorders differ in clinical presentation and classical neuropathology, converging evidence suggests that aberrant neuronal excitability and network dysfunction may represent a shared pathogenic pathway (Horvath et al., 2020).

In ASD, cortical hyperexcitability results from an imbalance between excitatory glutamatergic and inhibitory GABAergic signaling, leading to sensory hypersensitivity and seizure susceptibility (Bozzi et al., 2018; Takarae and Sweeney, 2017). Similarly, ADHD studies demonstrate altered excitatory-inhibitory control, often associated with hyperdopaminergic and glutamatergic network activity that disrupts attentional regulation and impulse control (Bauer et al., 2018). Over time, persistent neuronal hyperactivity may drive metabolic stress, calcium dysregulation, and oxidative damage, processes also observed early in neurodegenerative diseases such as Alzheimer’s (Muddapu et al., 2020). In AD, cortical and hippocampal hyperactivity are early features that progress to hypoactivity and neuronal loss as degeneration advances (Busche and Konnerth, 2015). Shared molecular pathways, including dysregulated Wnt/mTOR signaling and aberrant synaptic plasticity, further connect these conditions, suggesting a continuum from neurodevelopmental to neurodegenerative pathology (Grünblatt et al., 2023). Impaired glymphatic clearance and cerebrospinal fluid flow, as proposed in ASD and AD, may exacerbate excitability by allowing toxic protein accumulation (Phillips et al., 2025). In addition to mechanistic observations, the chronic excitatory state was also confirmed by clinical biomarkers in these disorders.

Patients with MCI, ASD, and ADHD frequently exhibit epileptiform discharges on electroencephalography (EEG) recordings, resting-state hyperactivity on functional magnetic resonance imaging (fMRI), and lower cortical excitability thresholds measured with transcranial magnetic stimulation (Takarae and Sweeney, 2017; Targa Dias Anastacio et al., 2022; Ugarte et al., 2023). In AD, subclinical epileptiform activity (SEA)—epileptiform discharges without overt clinical seizures—is increasingly recognized as a major contributor to accelerated cognitive decline (Kamondi et al., 2024; Vossel et al., 2026). Long-term EEG studies have demonstrated that SEA in AD is associated with faster cognitive deterioration and specific neuroanatomical substrates, including early precuneus thinning and larger general cortical volumes (Horvath et al., 2019; Nous et al., 2024). Previous observations have shown that sleep EEG is particularly sensitive to detect epileptiform activity in dementia (Horváth et al., 2017; Nous et al., 2024; Vossel et al., 2016). Some studies also suggest that SEA in dementia is associated with a special, probably more aggressive neuroimaging phenotype of AD (Cretin et al., 2016). Earlier reports have also demonstrated that SEA is linked to more rapid progression of cognitive decline in AD (Horvath et al., 2021; Vossel et al., 2013, 2016).

Beyond AD, SEA and other markers of cortical hyperexcitability are reported in ASD and ADHD, where they may relate to attentional deficits, learning problems, and behavioral disturbances (Lee et al., 2016; Spence and Schneider, 2009). Functional MRI studies in these populations describe hyperactivity and altered connectivity within key large-scale networks, including the default mode network (DMN), salience network (SN), and attention networks (AN), particularly early in the disease course (Hull et al., 2017; Konrad and Eickhoff, 2010). Some recent observations also suggest that the observed hyperactivity and connectivity changes may reflect an early excitatory/inhibitory (E/I) imbalance in preclinical AD (Fortel et al., 2023; Li et al., 2025; Ranasinghe et al., 2025). Based on these reports, some authors propose that multilevel changes in neural networks may be associated with a very early shift in E/I balance, a feature of AD pathology (Stam et al., 2023). A similar link between hyperactivity and hyperexcitability has been proposed in ASD (Port et al., 2019) and ADHD (Mamiya et al., 2021). However, disease-specific spatial differences in E/I imbalance have also been proposed as the primary involvement of the prefrontal cortex in ASD and ADHD (Ajram et al., 2017), and the DMN-specific imbalance in preclinical and prodromal AD (Giorgio et al., 2024). These commonalities suggest that ASD and ADHD may represent early-life manifestations of circuit-level dysregulation, while Alzheimer’s reflects its late-life degeneration (Pievani et al., 2011).

Despite this emerging evidence, several major knowledge gaps remain (Kamondi et al., 2024; Vossel et al., 2026): 1) There is no systematic, multimodal characterization of SEA and fMRI hyperactivity across MCI, ASD, ADHD and healthy aging within a unified protocol; 2) It is unclear to what extent hyperexcitability markers predict domain-specific cognitive impairment and neurodegeneration (atrophy, white matter damage); 3) The relationship between hyperexcitability, large-scale functional connectivity, sleep structure, sleep spindles, and memory consolidation is poorly understood; 4) Whether hyperexcitability modulates the burden or circadian dynamics of tau and amyloid-β pathology, particularly in prodromal AD, is unknown.

Addressing these gaps is essential for refining risk-stratification strategies for individuals at risk of cognitive decline and for designing targeted therapeutic approaches to modulate cortical excitability (Kamondi et al., 2024). In this paper, we highlight a study design to address these gaps, while the results of the ongoing study are not reported.

### Objectives and hypotheses

1.2

The overarching objective of the LENDÜLET Neurocognitive Research Project is to determine whether cortical hyperexcitability represents a common, mechanistically relevant substrate linking epileptiform activity to cognitive decline in aging and neurodevelopmental disorders. The LENDÜLET Research Grant is the most prestigious scientific grant of the Hungarian Academy of Sciences, awarded to establish individual working groups dedicated to research topics of extraordinary importance to public health and society’s strengths. We structure the project into two main work packages (outward clinical multimodal study, and in-ward mechanistic substudy), with the following specific aims and hypotheses.

Our working hypotheses are the following:

**Incidence of cortical hyperexcitability.**
*Hypothesis 1:* The incidence of cortical hyperexcitability (SEA on EEG, network-specific hyperactivity on resting-state fMRI) is significantly higher in MCI, ASD, and ADHD than in cognitively healthy controls.
**Association with cognitive performance.**
*Hypothesis 2:* Higher levels of cortical hyperexcitability are associated with poorer performance across standard neuropsychological measures of memory, attention, executive function, and visuospatial skills.
**Association with structural brain changes.**
*Hypothesis 3:* Hyperexcitability is associated with a distinct pattern of cortical volumes and white matter alterations on structural MRI, particularly in hippocampal, medial temporal, and parietal regions.
**Association with functional connectivity.**
*Hypothesis 4:* Hyperexcitability is associated with altered resting-state functional connectivity within and between DMN, SN, and AN, indicative of maladaptive network reorganization.
**Concordance across modalities.**
*Hypothesis 5:* There is significant cross-correlation between EEG-detected SEA and fMRI hyperactivity within the same individual.

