#### Sample size justification

2.2.4

Power calculations for the primary cross-sectional study were informed by previous investigations of cortical hyperexcitability and subclinical epileptiform activity (SEA) in neurocognitive disorders [summarized by Horvath et al. (2020)]. Assuming a medium effect size (Cohen’s *d* = 0.5), a two-sided significance level of α = 0.05, and four diagnostic groups, a sample size of 75 participants per group (total *N* = 300) provides more than 90% power to detect clinically meaningful between-group differences in the primary outcomes, including the incidence of SEA and resting-state fMRI hyperactivity.

The mechanistic in-ward substudy is enrichment-based and will include participants demonstrating evidence of cortical hyperexcitability. Assuming a conservative prevalence of approximately 15% across the clinical groups, we anticipate recruiting approximately 45 eligible participants, with an expected final sample of approximately 40 after accounting for an estimated 20% attrition rate.

The mechanistic substudy is designed primarily to characterize within-subject physiological relationships among cortical hyperexcitability, sleep architecture, memory consolidation, and circulating biomarkers using repeated-measures analyses. Because repeated observations substantially increase statistical efficiency for within-subject comparisons, this sample size is considered appropriate for estimating effect sizes, assessing feasibility, and identifying candidate mechanistic pathways. In contrast, more analytically demanding models, including formal mediation analyses and subgroup comparisons across diagnostic categories, are expected to have limited statistical power with the anticipated sample size. Accordingly, these analyses will be considered exploratory and hypothesis-generating, with emphasis placed on effect size estimation, confidence intervals, and model uncertainty rather than statistical significance alone. Findings from these exploratory analyses will inform sample size calculations and analytic strategies for future confirmatory multicenter studies.

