#### Cross-sectional analyses

2.6.1

Data from all diagnostic groups will be pooled into a single multivariate dataset and analyzed using machine learning and dimensional reduction techniques to extract cross-diagnostic patterns of neural and behavioral variance. The model will test for latent factors reflecting shared E/I imbalance across disorders, while *post hoc* analyses identify disorder-specific deviations. Statistical adjustments will account for confounders such as age, medication, and cognitive status.

Primary outcome will be the (Torenvliet et al., 2023) incidence and distribution of SEA, and fMRI hyperactivity in each diagnostic group relative to controls. Secondary outcomes will include relationships between hyperexcitability and (a) structural atrophy and white matter integrity; (b) functional connectivity within and between default mode, salience, and attention networks; (c) CSF and plasma tau/Aβ levels; and (d) domain-specific cognitive performance.

Incidence of hyperexcitability (primary outcome):○Logistic regression models comparing SEA and fMRI-positive status between groups (MCI, ASD, ADHD vs HC), adjusting for age, sex, education, and disease duration where applicable.○Results will be reported as odds ratios with 95% confidence intervals.

Associations with cognition, structure, and connectivity (secondary outcomes):○Within each group, participants will be classified as hyperexcitability-positive vs negative (see section “2.4.1 Participant selection and extraction of normative values”).○For continuous outcomes (neuropsychological scores, cortical thickness/volume, DTI measures, functional connectivity indices, blood-based biomarker concentrations), group comparisons will use *t*-tests or Mann–Whitney U tests depending on normality (Shapiro-Wilk).○For categorical variables, chi-square tests will be used.○Multivariable linear models with covariates (age, sex, education, disease duration, mood/anxiety scores) will assess independent associations.Holm–Bonferroni corrections will be used to control for multiple comparisons.

Cross-modal relationships:○Correlation and regression analyses will examine relationships between spike density and fMRI hyperactivity.○Multimodal latent variable models or clustering approaches will be applied exploratorily to define hyperexcitability phenotypes.

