Shared hyperexcitability phenotype across neurocognitive disorders. Elevated SEA incidence and resting-state fMRI hyperactivity in MCI, ASD, and ADHD, relative to healthy controls, would support the presence of cortical hyperexcitability as a transdiagnostic neurophysiological phenotype. Importantly, such findings would not imply that identical pathophysiological mechanisms underlie hyperexcitability across these disorders. Rather, they would suggest that distinct genetic, developmental, and neurodegenerative processes may converge on a common manifestation of disrupted excitation–inhibition balance and network dysfunction, while differing in their underlying molecular drivers, spatial distribution, temporal evolution, and contribution to cognitive impairment (Sohal and Rubenstein, 2019). Consequently, any commonality identified by this study should be interpreted as convergence at the systems-neuroscience level rather than evidence of a uniform disease mechanism.Network-level vulnerability. Associations between hyperexcitability and altered connectivity within the DMN, SN, and AN may clarify why specific networks are repeatedly implicated in both seizure susceptibility and cognitive dysfunction. For example, hyperactivity in posterior DMN hubs (precuneus, posterior cingulate) might simultaneously promote epileptiform discharges and disrupt memory-related network communication (Stam, 2014).Link between hyperexcitability and neurodegeneration. Demonstrating that hyperexcitability co-localizes with specific patterns of cortical thinning and white matter damage, particularly in medial temporal and parietal regions, would strengthen the hypothesis that recurrent SEA and network overactivity signal structural injury as well. In the MCI/AD continuum, associations with unfavorable tau/Aβ profiles would further support a bidirectional relationship between excitability and proteinopathy (Tanaka et al., 2025; Targa Dias Anastacio et al., 2022).Role of sleep and memory consolidation. Findings that hyperexcitability is associated with disrupted sleep architecture, altered N2/N3 power spectra, and reduced or disorganized sleep spindles, together with impaired overnight verbal memory consolidation, would provide a mechanistic bridge between epileptiform activity and long-term cognitive decline. This would be consistent with the view that sleep-dependent memory consolidation is particularly vulnerable to abnormal neuronal synchrony and that nocturnal SEA may exert disproportionate cognitive impact (Li et al., 2022; Slutsky, 2024).Cross-modal concordance. Evidence of concordance between EEG-detected SEA and fMRI hyperactivity at the individual level would validate the use of complementary modalities for detecting hyperexcitability and might enable future stratification strategies that rely on whichever modality is more feasible or sensitive in a given setting (Von Wegner et al., 2018).

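### Hypothesis 5 treats a significant EEG–fMRI correlation as concordance; a test of association cannot support the individual-level conclusion, which needs an agreement analysis of the two labels

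*Protocol article*

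**What the plan says.** All of this is in the protocol article.

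- **Section 1.2, Hypothesis 5.** The title is "Concordance across modalities". The hypothesis itself is "There is significant cross-correlation between EEG-detected SEA and fMRI hyperactivity within the same individual".
- **Section 2.6.1, cross-modal relationships.** "Correlation and regression analyses will examine relationships between spike density and fMRI hyperactivity". The latent-variable and clustering models listed next to it are exploratory. No minimum correlation and no EEG–fMRI agreement measure is given.
- **Section 3.2, cross-modal concordance.** "Evidence of concordance between EEG-detected SEA and fMRI hyperactivity at the individual level would validate the use of complementary modalities for detecting hyperexcitability", and this "might enable future stratification strategies that rely on whichever modality is more feasible or sensitive in a given setting".
- **Sections 2.3.3 and 2.3.4.** Each participant receives a positive or negative fMRI label and a positive or negative EEG label.
- **Sections 2.3.4 and 2.5.** Cohen's kappa with a 95% confidence interval is planned between EEG readers and for sleep staging, but not between EEG and fMRI.

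**The concern.** Correlation and agreement answer different questions. Rejecting a zero correlation shows that people with more spikes tend, to some degree, to have higher fMRI measures. It does not show that someone labelled positive by EEG is likely to be labelled positive by fMRI. The statement in section 3.2 about individuals, and still more the idea of relying on one modality alone, depends on the second property.

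If the study reports a small but significant correlation as confirming Hypothesis 5, its title and section 3.2 invite the reader to treat the modalities as concordant person by person. A later study that stratified on one modality could then miss most people whom the other would have flagged. Adjusting for diagnosis would not cure this, because an adjusted association is still only an association.

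**Working it through.** **Inputs from the protocol article.** There are 75 participants per group in four groups, so N = 300 (section 2.2.4), and section 2.6.1 pools all groups into one dataset. The two-sided 0.05 level is stated for the group comparison in section 2.2.4 and is assumed here for Hypothesis 5. The approximate 15% prevalence of hyperexcitability is also from section 2.2.4.

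**Assumptions.** The null hypothesis of zero correlation is implied by the word significant and is not written out. N = 300 is not stated for Hypothesis 5. The split of positives between modalities is not given, so 15% on each is an illustration and is varied below.

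**The plan's own figure.** None exists for Hypothesis 5. The only power statement (more than 90%) concerns between-group differences and has no bearing here.

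**Step 1: smallest significant correlation.** r = t / √(t² + N − 2).
- N = 300: t = 1.968, so r = 1.968 / √(3.873 + 298) = 0.113, and r² = 1.3%.
- One group of 75: t = 1.993, so r = 0.227, and r² = 5.2%.

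**Step 2: a significant 2x2 table.** Take 45 positive on each modality (15% of 300), with 12 positive on both.

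| | fMRI+ | fMRI− | Total |
|---|---|---|---|
| EEG+ | 12 | 33 | 45 |
| EEG− | 33 | 222 | 255 |
| Total | 45 | 255 | 300 |

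- Chi-square p = 0.017; Fisher exact p = 0.024.
- Observed agreement = (12 + 222)/300 = 0.780. Chance agreement = 0.15² + 0.85² = 0.745. Kappa = (0.780 − 0.745)/(1 − 0.745) = 0.14.
- Positive agreement = 2 × 12 / (45 + 45) = 0.27.
- 33 of 45 EEG-positives (73%) are fMRI-negative. Of the 78 people positive on either, 66 (85%) are discordant.

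**Step 3: other prevalences.** Section 2.4.1 defines hyperexcitability as positive on at least one modality, so the 15% may mean either. With 45 positive on either, 25 on each and 5 on both, phi = 0.127, chi-square p is about 0.03, and 40 of 45 (89%) are discordant. With phi held at 0.113 and the two prevalences varied between 5% and 30%, kappa is about 0.10 to 0.11, and 77% to 91% of those positive on either are discordant.

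**Step 4: a latent-score illustration.** Assume bivariate-normal scores with the top 15% positive on each modality. At latent r = 0.20 the probability of being positive on both is 0.0346.
- Overlap = 0.0346/0.15 = 23%.
- Kappa = (0.0346 − 0.0225)/(0.15 × 0.85) = 0.095.
- A correlation test on the continuous scores rejects with probability Φ(atanh(0.20) × √297 − 1.96) = 94%. A test on the binary labels rejects only about 37% of the time.
- At latent r = 0.50, kappa is still only 0.28.

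**Step 5: can agreement be estimated?** With 15% positive on each and N = 300, the standard error of kappa is about 0.073 at kappa 0.4 and 0.065 at kappa 0.6. The 95% intervals are about 0.26 to 0.54 and 0.47 to 0.73, which is precise enough to be informative.

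**The case against.** The strongest reply is that hypothesis and analysis match: Hypothesis 5 asserts a correlation and section 2.6.1 tests one, so only the title is wrong. That is true of the hypothesis sentence. It does not cover section 3.2, which draws a conclusion about individuals for which the protocol offers no other non-exploratory analysis.

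Several further points stand and limit the finding:

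- **Interchangeability is not claimed outright.** A reader might infer that any significant correlation would validate substituting one modality for the other. The text does not say so. The validation in section 3.2 attaches to complementary use, reliance on one modality is worded only as something that might follow, and section 3.2 does not state that a p-value is what counts as evidence of concordance.
- **No decision in this study replaces one modality with the other.** Entry to the in-ward substudy requires positivity on at least one of them (section 2.4.1). Concordance is not among the listed primary or secondary outcomes.
- **This is not inflated type I error.** It is tempting to set the 94% in Step 4 against a nominal 5%. But 94% is power when the true correlation is 0.20, and Hypothesis 5 as worded is then true. It also belongs to a test on continuous scores, whereas kappa describes the binary labels.
- **Kappa thresholds from rater agreement are not supported.** Nothing in the protocol justifies a bound such as 0.4 to 0.6 for two different physiological signals.

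The choice of an agreement statistic could sit in an analysis plan that is not shown. However, the hypothesis, the form of its test and the interpretation are all fixed in the article, and a plan that followed them would carry the mismatch forward. Holm–Bonferroni correction or within-group testing would raise the critical r, but the test would remain one of zero association.

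**Conclusion.** The point holds in this form: the stated test supports a statement of association only, while the title of Hypothesis 5 and section 3.2 speak of concordance, in the latter case in individuals. At N = 300 a correlation of about 0.113 is enough for significance, and a significant table can have kappa of 0.14 with 73% of EEG-positives negative on fMRI. These figures rest on the pooled N, a two-sided 0.05 test and the assumed prevalences. Low agreement at the significance threshold persists across prevalences of 5% to 30%.

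A reader might go further and infer that the modalities do label different people. The protocol contains no data on this. A significant correlation is compatible with poor agreement and equally with good agreement, which is why it cannot settle the matter. The issue concerns a named hypothesis and its interpretation, not the primary outcome.

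**What to change.** In section 2.6.1, add the 2x2 table of EEG-positive by fMRI-positive status, with Cohen's kappa and positive agreement (or the overlap in each direction) and 95% confidence intervals, overall and by diagnosis. State that any conclusion about concordance in individuals, or about using one modality alone, will rest on those estimates. Keep the correlation and regression as evidence of association only. Retitle Hypothesis 5 as an association between modalities, or add the agreement estimate to it, and reword the cross-modal sentence in section 3.2 to match. If the sponsor wants a threshold for claiming concordance, it should be stated in advance with its own justification.

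The cost is one table from labels the study already plans to produce, plus wording changes; no new data are needed. Estimates by diagnosis will be imprecise with 75 per group. The concordance claim becomes harder to reach.
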